## Outcome measures

4

### Primary outcome

4.1

The primary outcome in this trial is the Mayo score at baseline, after an 8-week intervention, and 3-month remission period maintenance therapy.

The Mayo score scoring standard is based on references^[38]^ (Table 2). A total score of <2 is divided into symptom relief, 3 to 5 is divided into mild activity, 6 to 10 is divided into moderate activity, and 11 to 12 is divided into severe activity.

**Table 2 T2:** Mayo scoring system for assessment of ulcerative colitis activity.

Score	Stool frequency A	Bloody stools B	Colonoscopy	Physician's global assessment C
0	Norma (no. of stools for this patient)	No blood seen	Normal or inactive disease	Normal
1	1–2 times more than normal	Streak of blood with stool less than half the time	Mild disease (erythema, decreased vascular pattern, mild friability)	Mild
2	3–4 times more than normal	Obvious blood with stool most of the time	Moderate disease (marked erythema, lack of vascular pattern, friability, erosions)	Moderate
3	5 or more times more than normal	Blood alone passes	Severe disease (spontaneous bleeding, ulceration)	Severe

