### Participants

2.3

A total of 236 women in the child-bearing period with UC will be recruited after signed the informed consent. They will be invited to the Department of gynecology, Teaching Hospital of Chengdu University of Traditional Chinese Medicine. The printed recruitment posters will be post in the hospital to recruit participants. All participants should meet the diagnostic criteria according to the Chinese consensus on the diagnosis and treatment of IBD.^[34]^ Eligible participants will be implemented randomly with a 1:1 allocation ratio in the control group with (n = 118) or the experimental group (n = 118).

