### Sample size

2.6

The sample size was determined by the primary study results. According to previous reports, the effective rate of the experimental group based on the Mayo, score ranges from 57.5% to 76.47%,^[35,36]^ and the average rate is about 66.99%. The effective rate of the control group ranges from 41.25% to 55.65%,^[22,37]^ and the average rate is about 48.45%. We will use the following formula to estimate sample size:$${\text{n}}_{\text{c}}=\frac{[\pi_{t}(1-\pi_{t})/k+\pi_{c}(1-\pi_{c})]{\left(u_{1-\partial /2}+u_{1-\beta }\right)}^{2}}{{\left(\pi_{t}-\pi_{c}\right)}^{2}}$$

With a 5% significance level (α = 0.05), 80% Power (β = 0.2), and 10% dropout rate, at least 118 patients should be enrolled in each group and 236 total participants will be recruited.

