### Statistical analysis

4.5

The statistician performs Statistical analyses of data by using SPSS21.0 software (International Business Machines Corp., Armonk, NY). Intention-to-treat principle approach for efficacy and safety analysis will be used. As dealing with the missing values, multiple imputations method will be applied. Continuous variables with normal distribution, expressed as Mean ± Standard Deviation, will be analyzed by *t* test. In contrast, nonparametric tests will be adopted when variables are kept in the abnormal distribution. Categorical data presented by frequency and percentage will be analyzed by the chi-square test or Fisher exact test. All the tests will be conducted two-sided, and a *P*-value < .05 will be considered as the significant level.

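### The 80% power is calculated for an undefined Mayo-based effective rate, not for the Mayo score named as primary, and no single primary time point is set

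*Protocol article*

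**What the plan says.** **Primary outcome (section 4.1).** "The primary outcome in this trial is the Mayo score at baseline, after an 8-week intervention, and 3-month remission period maintenance therapy". The section then bands the total score into symptom relief and mild, moderate or severe activity. It names no change score, no responder definition and no single primary time point.

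**Sample size (section 2.6).** The calculation compares two proportions. For the experimental arm, "the effective rate of the experimental group based on the Mayo, score ranges from 57.5% to 76.47" per cent, "and the average rate is about 66.99" per cent. For the control arm the range is 41.25% to 55.65%, "and the average rate is about 48.45" per cent. With two-sided alpha 0.05, 80% power and "10% dropout rate, at least 118 patients should be enrolled in each group and 236 total participants will be recruited". No cut-off or time point is given for the effective rate.

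**Other outcomes (sections 4.2 and 4.3).** The listed rates are pregnancy, abnormal pregnancy, live birth and mucosal healing. An effective rate is not among them.

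**Analysis (section 4.5).** Normally distributed continuous variables go to a t test, other continuous variables to a nonparametric test, and categorical data to chi-square or Fisher. "All the tests will be conducted two-sided" and judged at P < .05. The approach is intention to treat.

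**Interventions (section 3).** After week 8, maintenance therapy is described for patients in remission.

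**The concern.** The quantity that justifies 236 women should be the quantity on which the trial is judged. Here one section uses a proportion and another uses a score, and nothing in the article converts one into the other. A reader who sees 80% power will attach it to the Mayo score, for which the article gives neither a mean difference nor an SD.

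The list of time points leaves a second choice open. Baseline cannot show a treatment effect, so two post-baseline comparisons remain: week 8 and the end of maintenance. The article does not say which one decides the trial, or whether one or both must be significant.

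At stake is whether the primary claim is fixed in advance. As written, score or rate, and week 8 or end of maintenance, could be settled after the data are seen.

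**Working it through.** **1. Reproduce the stated size.** Inputs from section 2.6: π_t = 0.6699, π_c = 0.4845, two-sided alpha 0.05, power 0.80, dropout 10%. From section 2.3: 1:1 allocation, so k = 1.

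n = [π_t(1 − π_t)/k + π_c(1 − π_c)] × (1.960 + 0.842)² / (π_t − π_c)²

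= (0.2211 + 0.2498) × 7.849 / 0.1854²

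= 0.4709 × 7.849 / 0.03437 = 107.5 per group.

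107.5 × 1.1 = 118.3, which is the stated 118 after rounding down. Dividing by 0.9 instead gives 120. The arithmetic is sound to within two women per group, and it is arithmetic for a difference in proportions.

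**2. Power of the present size for that rate.** 118 less 10% leaves 106 evaluable per arm. SE = √(0.4709/106) = 0.0667; 0.1854/0.0667 = 2.782; power = Φ(2.782 − 1.960) = 79.4%. With a pooled variance it is 78.4%.

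**3. Power for the Mayo score.** This cannot be computed from the article. What can be stated is the standardised difference detectable with 106 per arm at 80% power:

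2.8016 × √(2/106) = 0.385 SD.

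Over an assumed range of true differences, power is 31% at 0.2 SD, 59% at 0.3, 83% at 0.4 and 95% at 0.5.

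**4. What the plan's own rates might imply for the score.** Assume that effective means falling on one side of a cut on a roughly normal score (or change in score) with equal SDs. The implied shift is then Φ⁻¹(0.6699) − Φ⁻¹(0.4845) = 0.440 + 0.039 = 0.478 SD. With 106 per arm, power = Φ(0.478 × √53 − 1.960), about 94%; at a two-sided level of 0.025 it is about 89%.

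**5. Two post-baseline tests.** If success at either would count, the false-positive rate with both nulls true is P(|Z₁| > 1.96 or |Z₂| > 1.96) for bivariate normal statistics:

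| Correlation | Rate |
|---|---|
| 0 | 1 − 0.95² = 9.75% |
| 0.5 | 9.1% |
| 0.8 | 7.8% |

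If both must be significant, the rate does not exceed 5%. If either suffices and Bonferroni is applied (0.025 each), the effective-rate calculation needs 131 evaluable, or 146 enrolled, per group; 106 evaluable would give 70.5% power.

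**6. Who contributes at the later time.** Section 3 takes women in remission at week 8 into maintenance, and treats those whose symptoms have not eased as excluded cases who are still asked to complete assessments as far as possible. Table 1 schedules a Mayo score in weeks 9–20 without naming a subset. The end-of-maintenance comparison may therefore rest largely or wholly on women selected after randomisation, and fewer than were sized for. The rates in step 5 treat both comparisons as made in the same randomised groups.

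**The case against.** **The two quantities are related.** Section 2.6 ties the effective rate to the Mayo score, and section 4.1 bands that score, so a categorical analysis by chi-square would be within the plan. This stands as far as it goes: the instrument is the same. But no band is labelled effective and no threshold for change is given, so the step from score to rate is still missing.

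**The trial may have ample power for the score.** A reader might infer from the mismatch that the trial is underpowered. The documents do not support that. Under the assumption in step 4, power for the score is about 94%, and the detectable 0.385 SD is smaller than the implied 0.478 SD. What remains is that the stated 80% is not a statement about the named outcome.

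**The time points may be only a measurement schedule.** A reader might infer that the trial runs at a false-positive rate near 10%. That would need a rule that either time point suffices, and the article states no such rule. The list includes baseline, and section 4.5 gives a general threshold without a sentence on the Mayo time points. The 7.8% to 9.75% is therefore conditional.

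**An analysis plan could supply the detail.** Multiplicity rules and baseline adjustment are often left to it. But an analysis plan cannot make the power statement in section 2.6 apply to a different outcome in section 4.1; those two sections must agree with each other.

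**Conclusion.** The concern holds in this form: the sample size and 80% power in section 2.6 are for a Mayo-based rate with no stated cut-off or time point, while section 4.1 makes the Mayo score itself primary and does not single out one time point. The stated power does not belong to the named primary outcome.

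Power for the score is unstated, not shown to be low. The 94% figure rests on normality, equal SDs and a single cut, none of which the article confirms.

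The false-positive rate is about 7.8% to 9.75% only if success at either post-baseline time counts, with correlation between 0.8 and 0 and the same women at both times. It is not inflated if both must succeed. That the article leaves this open is the defect; it does not establish that the error rate is raised.

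The possible restriction of the later comparison to week-8 remitters is a further reason to place the primary claim at week 8.

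**What to change.** Name one primary endpoint at week 8, compared in all randomised women at two-sided 0.05, and make sections 2.6, 4.1 and 4.5 agree on it. Either option resolves the mismatch:

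- **(a) A Mayo-based effective rate** with a cut-off written into the protocol itself, tested by chi-square. The definition should not be borrowed by reference from the four cited reports, since nothing in the article shows that they share one. The present size then gives about 79% power with 106 evaluable per arm under the stated rates.
- **(b) The week-8 Mayo score adjusted for baseline.** Replace the power statement in section 2.6 with 80% power for a difference of about 0.38 SD with 106 evaluable per arm, and add the adjusted analysis to section 4.5, which now names only unadjusted tests for continuous variables.

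Under both, make the post-maintenance Mayo result secondary, say which women it covers, and treat baseline Mayo as a covariate, not an outcome.

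The cost is small but is more than a wording change. Section 5.1 says recruitment began on October 30, 2020, so this should be a dated amendment made before unblinding, with the registry entry brought into line if it differs. Neither option needs more women if about 79% power under (a), or the detectable difference under (b), is acceptable. The post-maintenance result can no longer carry the primary claim.

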### Secondary outcomes

4.2

The secondary outcomes include:

1.pregnancy outcomePregnancy outcome include pregnancy rate (%), abnormal pregnancy rate (%), and live birth rate (%). In this study, abnormal pregnancy is defined as any of the following: abortion, threatened abortion, premature delivery, delivery of a low-birth-weight infant, VTE, and congenital defect, etc—any pregnancy-related event causing illness in the mother or fetus.2.mucosal healing rate (%)Patients with remission UC can be seen as normal colon mucosal appearance, pseudopolyp formation, or scar-like changes.3.IBDQThe patients’ quality of life is evaluated by the IBDQ^[39]^ included the 32 items and divided into 4 modules: bowel symptoms, systemic symptoms, emotional function, and social function. Each question has graded responses from 1 to 7, and thus scored from 32 to 224 points, with a higher score indicates a better quality of life.4.FCEndoscopies as the “gold standard” determine the presence of mucosal inflammation in the bowel. Some studies propose that endoscopy should be used with caution during pregnancy to avoid adverse pregnancy outcomes.^[40,41]^ Therefore, for the noninvasive monitoring of the activity or relapse of UC, the FC will be measured to replace endoscopyat after pregnancy. The concentration of FC has a strong correlation with the level of intestinal inflammatory activity during pregnancy.^[42]^

### Safety outcomes

4.3

KFX has been used clinically for many years and has satisfactory safety profiles. To monitor the adverse reactions, Safety evaluation will include electrocardiogram, routine examination, blood routine test, hepatic function, renal function, urine routine test, and stool routine test. All safety results will be evaluated at baseline, 8th, 20th week after the intervention, 0th, 4th, 7th month, and until delivery after pregnancy.

If any adverse event occurs including toxicity and side effects, researchers should record it in the case record form (CRF) in detail and provide a proper treatment emergently. A serious adverse event will be reported to the ethical committee within 24 h. In addition, the patient will be determined whether to terminate the trial based on the severity.

### Quality control and trial monitoring

4.4

In order to maintain the quality of the study, all researchers will accept specialized training including how to select and exclude participants, how to correctly manipulate intervention measures, how to fill the case report forms uniformly, how to evaluate outcomes, and manage data. The trial data of the patient will be recorded in the case record and then input into the spreadsheet respectively by 2 data managers. Once the CRF is completed, the data will be locked and not to be allowed to modify. To guarantee the objectivity of the data, the data managers submit it to the statistician for statistical analysis blinded during the trial.

### Statistical analysis

4.5

The statistician performs Statistical analyses of data by using SPSS21.0 software (International Business Machines Corp., Armonk, NY). Intention-to-treat principle approach for efficacy and safety analysis will be used. As dealing with the missing values, multiple imputations method will be applied. Continuous variables with normal distribution, expressed as Mean ± Standard Deviation, will be analyzed by *t* test. In contrast, nonparametric tests will be adopted when variables are kept in the abnormal distribution. Categorical data presented by frequency and percentage will be analyzed by the chi-square test or Fisher exact test. All the tests will be conducted two-sided, and a *P*-value < .05 will be considered as the significant level.

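### Continuous outcomes are compared without using the baseline values the trial collects: valid, but it gives up precision that costs nothing to keep

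*Protocol article*

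**What the plan says.** Section 4.5 (Statistical analysis) sets one rule for all continuous variables. "Continuous variables with normal distribution, expressed as Mean ± Standard Deviation, will be analyzed by" a t test; otherwise, "nonparametric tests will be adopted when variables are kept in the abnormal distribution". The nonparametric test is not named. Categorical data go to a chi-square or Fisher exact test, and "All the tests will be conducted two-sided". The section names no covariate, no ANCOVA, no mixed model and no change score, and no other section does.

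The baseline values exist. Table 1 marks Mayo score, IBDQ and faecal calprotectin at the screening visit, four weeks before treatment. Section 4.1 opens with "The primary outcome in this trial is the Mayo score at baseline" and then adds the 8-week and post-maintenance time points, so the baseline Mayo score is named within the primary outcome itself.

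Section 2.7 describes allocation from a computer-generated random list and states no stratification.

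**The concern.** When an outcome is measured before and after treatment, the baseline value usually explains part of the spread in the follow-up value. A t test or rank test on follow-up values treats that spread as noise. The confidence interval is wider than it need be, and power is lower for the same number of women. With no stratification stated, the design does not account for baseline severity either.

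What is at stake is precision for the Mayo score, IBDQ and calprotectin. Section 4.5 states the method, so this is a choice the document makes rather than a detail it leaves open.

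**Working it through.** **Inputs from the document.** Section 2.6: "With a 5% significance level (α = 0.05), 80% Power (β = 0.2), and 10% dropout rate"; experimental arm, "the average rate is about 66.99" percent; control arm, "the average rate is about 48.45" percent; 118 per arm. Section 2.3: "Eligible participants will be implemented randomly with a 1:1 allocation ratio", so k = 1. Section 4.5: two-sided tests.

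**Input not in the document.** r, the correlation between baseline and follow-up values. It is assumed, from 0.1 to 0.5.

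**Step 1: reproduce the stated sample size.** From the formula in section 2.6:

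n = [0.6699 × 0.3301 + 0.4845 × 0.5155] × (1.960 + 0.842)² / (0.6699 − 0.4845)² = 107.53 per arm.

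107.53 × 1.10 = 118.28, which matches 118. Dividing by 0.90 instead gives 119.5, within two patients. The sample size is not at fault here. It is a calculation for two proportions.

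**Step 2: evaluable women.** 118 × 0.90 = 106.2, so about 106 per arm and 212 in total.

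**Step 3: a reference continuous comparison.** The document states no power for a difference in mean Mayo score, so one has to be set up. With 106 per arm, an unadjusted t test has 80% power for a difference of 2.802 × √(2/106) = 0.385 SD.

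**Step 4: effect of adjustment.** ANCOVA multiplies the residual variance by 1 − r². Power becomes Φ(2.802/√(1 − r²) − 1.960), and the equivalent number of women is 212/(1 − r²).

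| r (assumed) | 1 − r² | Power with ANCOVA | Equivalent women |
|---|---|---|---|
| 0.1 | 0.99 | 80.4% | 214 |
| 0.2 | 0.96 | 81.6% | 221 |
| 0.3 | 0.91 | 83.6% | 233 |
| 0.4 | 0.84 | 86.4% | 252 |
| 0.5 | 0.75 | 89.9% | 283 |

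**Step 5: simulation check.** 3,000 trials per setting, 106 per arm, normal data, true difference 0.385 SD. The switching rule was represented by a Shapiro check leading to a t test or a Mann-Whitney test.

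| r | t test | t or rank by Shapiro check | Change-score t test | ANCOVA |
|---|---|---|---|---|
| 0.3 | 80.9% | 80.8% | 65.6% | 84.1% |
| 0.5 | 79.2% | 79.1% | 80.0% | 89.0% |
| 0.7 | 79.3% | 79.1% | 94.4% | 97.1% |

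With no true difference, rejection rates were 4.7% to 5.9% across all four methods. The r = 0.7 row lies outside the assumed range and shows only the direction.

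**Step 6: change scores.** With equal variances at the two times, a change score has relative variance 2(1 − r). Since 2(1 − r) − (1 − r²) = (1 − r)², which is never negative, ANCOVA is at least as precise as a change-score test at any r. It is also at least as precise as the unadjusted test, because 1 − r² never exceeds 1. The price is one degree of freedom (209 instead of 210), which is negligible.

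**The case against.** The strongest reply is that this is a preference about efficiency and not an error. Much of it stands.

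- **Validity.** A reader might infer that the unadjusted estimate is biased, or that chance imbalance makes it unreliable. The document does not support that. Under randomisation the test is unbiased, its standard error already allows for chance imbalance, and simulated type I error stayed near 5%.
- **Switching between tests.** A reader might infer that choosing the test from the observed distribution distorts the error rate. No such harm was shown: in the simulation the switch performed like the plain t test. Those were normal data only, so this does not clear the rule for skewed data. A rank test is also defensible for a bounded 0 to 12 score.
- **Low correlation.** It is tempting to say that baseline Mayo varies widely and predicts follow-up. The text gives no source for either. Entry rests on a consensus document not shown, active disease in section 4.1 starts at 3, the baseline is taken four weeks before treatment, and only women in remission go on to maintenance. All of this may put r for Mayo at the low end, where the gain is negligible (80.4% at r = 0.1).
- **Change scores.** Section 4.5 does not say whether the t test is on follow-up values or on change, and section 4.1 names the baseline. A change score would recover part of the loss at high r, but does worse than the plain t test at r = 0.3.
- **Left to an analysis plan.** Covariates often are. Here, however, the article states the test, and as stated it uses no baseline.

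A low r shrinks the benefit without creating a downside, so the point survives in modest form.

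**Conclusion.** The point holds as a loss of precision in the stated analysis. For assumed r from 0.1 to 0.5 it ranges from negligible (variance factor 0.99) to material (0.75). The figures rest on the assumed r, on a linear model for a continuous outcome, and on about 212 evaluable women.

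Two larger claims should not be drawn from them. First, a reader might infer that the trial's own 80% power would rise to as much as 90%. That 80% belongs to a comparison of two proportions, whereas the power column illustrates a continuous comparison set to 80% by construction; no gain was computed for the effective rate. Second, the equivalent numbers should not be scaled from the 236 enrolled, because that total includes the 10% dropout allowance.

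This is a worthwhile improvement to the analysis wording. It does not threaten the validity of the trial's conclusions.

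**What to change.** In section 4.5, replace the t test or nonparametric rule for Mayo, IBDQ and calprotectin with a pre-specified ANCOVA of the follow-up value on treatment and the baseline value, with calprotectin on the log scale. Report the adjusted difference with its 95% confidence interval, and keep a named rank test as a sensitivity analysis. If the effective rate is what is tested, adjust it for baseline Mayo, for example by logistic regression, and report a standardised risk difference.

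The cost is a change of wording, made before unblinding. The baseline values are already collected, SPSS fits these models, and the sample size stays at 118 per arm. The ANCOVA coefficient and its standard error can also be pooled directly across the multiple imputations that section 4.5 plans.

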## Discussion

5

Up to now, the etiology of UC has not been fully elucidated. Genetics, environmental factors, autoimmunity, and gut microbiota are generally considered to be key risk factors for UC. Research by analyzing the intestinal bacterial community indicates that UC patients have intestinal dysbiosis with reduction of biodiversity,^[43]^ In particular, Firmicutes and Bacteroidetes known to promote gut health have been reduced most significantly.^[44]^ Moreover, the impaired epithelial barrier is caused by key pro-inflammatory cytokines (tumor necrosis factor-α (TNF-α, interferon (IFN)-γ, interleukin (IL)-13, etc)is a pathogenic factor for UC.^[45,46]^ In recent years, Mitochondriopathy is considered to be the pathogenic process in UC, loss of mitochondrial homeostasis brings about defective energy production, increased mitochondrial oxidative stress, and the release of pro-inflammatory DAMPs1 molecular.^[47–50]^

Generous studies based on UC mouse models trials show that Periplaneta americana increases the Lactobacillales in UC mouse, decreases *E coli* intestinal bacteria translocation, modulate the flora structure, restore the intestinal-immune system, stimulate fibroblasts proliferation and accumulate collagen significantly to promote the colonic morphology and mucosal barrier recovery.^[30–32,51]^ Simultaneously, Periplaneta americana improves the accumulation of myeloperoxidase (malondialdehyde, superoxide dismutase, catalase, and nitric oxide), reduce inflammatory factor expression (TNF-a, IL-6, MMP-9, and MMP-2 ), and block the MAPK/NF-κB signaling pathway.^[29]^ Currently, high-quality research and evidence are lacking in KFX for the female with fertility requirements. Therefore, we conduct a randomized and controlled trial to evaluate the efficacy and safety of mesalazine combined with KFX enema before pregnancy in the treatment of active UC in women with fertility requirements and to improve pregnancy outcome and quality of life, reduce the recurrence rate. In particular, we use the FC instead of endoscopic examination which is not be suggested to be used to assess the symptom progression of the UC during the pregnancy. We hope the results clarify the value of KFX as the adjunctive therapy for a child-bearing period female with active UC.

